### Current study

Our research group has developed a traditional transdiagnostic treatment that is partly based on the UP [37]. Taking into account the importance of emotion regulation in the treatment of ED, it also includes components of emotion regulation from DBT [52]. Based on the traditional treatment protocol, we developed EmotionRegulation, an adaptation of this treatment that can be applied online over the Internet.

In this study, we aim to present EmotionRegulation, and test its effectiveness for the treatment of ED in an RCT with a sample made up of participants from specialized care in the Spanish public mental health system, compared to TAU. The ED targeted in this study will be major depression disorder (MDD), dysthymic disorder (DD), panic disorder (PD), agoraphobia (A), social anxiety disorder (SAD), generalized anxiety disorder (GAD), and obsessive-compulsive disorder (OCD). Anxiety disorder not otherwise specified (ADNOS) and (unipolar) mood disorder not otherwise specified (MDNOS) will also be targeted. Secondary objectives will include the following: a) study of the effects of EmotionRegulation on two dimensions of temperament (that is, N/BI and E/BA) and b) study of the acceptability (expectations and opinions) of the online program by patients. In this article, we present the study design.

## Methods/Design

### Study design

A two-armed simple-blinded randomized controlled trial will be conducted. Participants will be randomly allocated to one of two conditions: a) EmotionRegulation and b) TAU. Randomization will be stratified by primary diagnosis. Block randomization will be performed within each strata in order to ensure all primary diagnoses are equally represented across conditions. The study will be conducted following the CONSORT statement (Consolidated Standards of Reporting Trials, http://www.consort-statement.org) [75, 76] and CONSORT-EHEALTH guidelines [77]. Participants will be assessed at pre- and post-treatment, and at 3- and 12-month follow-ups. The study flowchart is shown in Fig. 1.

**Fig. 1 Fig1:**
[figure not shown]
Study flowchart. EmotionRegulation, transdiagnostic Internet-based protocol; TAU, treatment as usual

### Study population

The clinical trial will be conducted in the Mental Health Department of the Provincial Consorcio Hospitalario in Castellon and the University Hospital La Ribera in Valencia (Spain). Participants will be adult outpatients from specialized care who attend mental health units to seek psychological and/or psychiatric treatment. Participants will be recruited by clinical psychologists and psychiatrists working in these centers, until the required sample is complete. In order to facilitate the selection of participants in the study, both clinical psychologists and psychiatrists will be given a sheet containing the eligibility criteria.

### Ethics

This trial will be conducted in compliance with the study protocol, the Declaration of Helsinki and good clinical practice. Data security/confidentially will be guaranteed; all relevant EU legislation and international texts on privacy will be observed and respected. Access to the Internet platform is through a unique username-password combination and will be available on a 24/7 basis. All transferred data will be secured via AES-256 encryption.

The study has been approved by the Ethics Committee of University Jaume I (Castellon, Spain) and the Clinical Research Ethics Committee from two hospitals (Consorcio Hospitalario Provincial de Castellon, and Hospital Universitario de la Ribera). The trial was registered at clinicalstrials.gov as NCT02345668. For ethical reasons, patients allocated to TAU will be offered free access to EmotionRegulation after the study has been completed.

### Eligibility criteria

Inclusion criteria will include the following: a) be 18 years or older; b) ability to understand and read Spanish; c) access to Internet at home and having an email address; d) meeting the DSM-IV diagnostic criteria [78] for ED (MDD, DD, MDNOS, PD, A, SAD, GAD, ADNOS, OCD); and e) providing written, informed consent. Exclusion criteria include the following: a) suffering from a severe mental disorder (schizophrenia, bipolar disorder, and alcohol and/or substance dependence disorder); b) the presence of a high risk of suicide; c) medical disease/condition that prevents the participant from carrying out the psychological treatment; or d) receiving another psychological treatment during the study in the experimental group. Receiving pharmacological treatment is not an exclusion criterion during the study period, but patients having an increase and/or change in the medication 2 months prior to enrollment will not be considered for the trial. Also, the increase and/or change in the medication during the study period in the experimental group will imply the participant’s exclusion from subsequent analyses (a decrease in pharmacological treatment is accepted).

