### Recruitment

When the psychiatrist or clinical psychologist identifies a potential participant, he or she will describe the study characteristics to him/her. Those candidates interested in participating will sign an informed consent, and the professional will fill out a document describing the participant’s sociodemographic and clinical characteristics, and give him/her a patient information sheet and a handout describing the study. After confirming that the participant has signed the informed consent and understands the study and the treatment options, the researcher will administer assessment instruments related to the inclusion criteria. If the patient fulfills all the study criteria, the researcher will contact an independent researcher to implement randomization. Participants who meet all the inclusion criteria will then be randomized to either EmotionRegulation or TAU and complete the remaining assessment instruments. Participants will be free at any time to withdraw from the treatment or the study without giving any explanation.

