### Randomization and blinding

Patients will be randomly allocated in a 1:1 ratio to either of the two groups (EmotionRegulation or TAU) using a computer-generated random number sequence. The Epidat 4.1 program will be used to generate this sequence. The allocation will be carried out by an independent researcher who will be unaware of the characteristics of the study. The sequence will be concealed until interventions are assigned. Patients will agree to participate before the random allocation and without knowing to which treatment they will be allocated. Study researchers conducting psychological assessments (that is, diagnostic interviews) throughout the entire study will be masked to the participants' treatment conditions and unaware of the treatment group to which the patient belongs. For ethical and practical reasons, participants will not be blind to the treatment conditions.

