
These modules are sequential, in order to move through the program step by step. The program duration can vary among the users, and it is estimated that for most participants the duration will be 18 weeks. During the study, EmotionRegulation will be accessible only to participants in the online intervention group. Participants will be allowed to use the program at any time they want during the trial period. See Table 2 for other functionalities in EmotionRegulation.

**Table 2 Tab2:** Other functionalities in EmotionRegulation

a) Assessments: The program allows the pre-, post- and follow-up instruments to be completed online.	
b) Module self-assessments: Each module ends with a short list of multiple-choice questions that allow participants to assess their understanding of the module and help them to decide whether they need to review its contents.	
c) Automatic e-mails with reminders when participants have not accessed the program in the past 15 days.	
d) Suicide risk alarms: Therapists receive warnings of participants with high risk of suicide (when participants answer questionnaires that include items assessing high suicide risk)	
e) Post-module questionnaires: Each module includes three brief questionnaires (OASIS, ODSIS and PANAS) to evaluate anxiety, depression and positive/negative affect after each treatment module. Participants are able to monitor these scores in the feedback section through the ‘How am I?’ button.	
f) Printable documents: Each module contains several printable documents (PDF) with summaries and self-monitoring sheets that participants are encouraged to use to practice the skills and strategies.	

Participants in the EmotionRegulation condition will be allowed to maintain medication if there are not changes and/or increases but will not be allowed to receive another psychological treatment during the study period. Failure to fulfill these criteria will result in the participant’s data being excluded from data analysis.

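### Exclusion criterion d) depends on the allocated arm and on later treatment, so it cannot be assessed before randomisation; as written it is an EmotionRegulation-only restriction with data removal, which conflicts with intention to treat

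*Protocol article*

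**What the plan says.** All references are to the protocol article.

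- **Eligibility criteria.** Exclusion d) is "receiving another psychological treatment during the study in the experimental group". The same paragraph contains a medication rule that looks back from enrolment and applies to everyone: "patients having an increase and/or change in the medication 2 months prior to enrollment will not be considered for the trial". It then adds that a medication increase or change during the study, in the experimental group, removes the patient from later analyses. Decreases are accepted.
- **Study population.** Participants are outpatients "who attend mental health units to seek psychological and/or psychiatric treatment". For screening, "both clinical psychologists and psychiatrists will be given a sheet containing the eligibility criteria".
- **Recruitment.** "If the patient fulfills all the study criteria, the researcher will contact an independent researcher to implement randomization".
- **Randomization and blinding.** The sequence is concealed until assignment, and patients agree to take part "without knowing to which treatment they will be allocated".
- **Interventions, EmotionRegulation.** Participants in this arm "will not be allowed to receive another psychological treatment during the study period". The consequence follows: "Failure to fulfill these criteria will result in the participant’s data being excluded from data analysis".
- **Interventions, TAU.** TAU can include psychological treatment, and patients already receiving it carry on. No removal rule is given.
- **Analysis.** Primary and secondary outcomes at post-treatment and both follow-ups are to be analysed by intention to treat with mixed models. A per-protocol analysis is planned separately.

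**The concern.** An exclusion criterion has to be answerable for every candidate at screening. Criterion d) asks two things that nobody can know then: which arm the patient will be in, and what treatment the patient will receive afterwards. It nevertheless belongs to the list that clinicians are given for selecting participants.

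What the rule does after randomisation matters more. It applies in one arm and carries removal from the analysis. People attending these units are looking for treatment, so some EmotionRegulation patients may keep or start other therapy. If they are dropped while comparable TAU patients are analysed, the two groups are no longer those that randomisation formed. The direction of the resulting bias is open. Dropping patients who sought therapy because they were doing badly would favour EmotionRegulation. Dropping patients whom the extra therapy helped would work against it.

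**Working it through.** **Step 1: can d) be assessed when eligibility is decided?**

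| What d) needs to know | When it becomes known | Source |
|---|---|---|
| Whether the patient is in the experimental arm | At assignment, after eligibility is settled | Recruitment; Randomization and blinding |
| Whether other psychological treatment is received during the study | After enrolment | Wording of d) itself |

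Neither is available at screening, so no candidate can be scored on d).

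**Step 2: could d) be a general entry bar on current therapy?** No. It is limited to one arm and to the study period, and the TAU section expects some patients to be in psychological treatment on entry and to continue it. Read together, the sections admit patients in current therapy.

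**Step 3: where does d) take effect?** In the EmotionRegulation section, as a ban followed by data exclusion for those who break it. TAU has no counterpart. The exclusion is not limited to the per-protocol analysis, so it stands against the intention-to-treat commitment in the Analysis section.

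**Step 4: how large could the effect be?** The plan gives no figure for this, so there is none to reproduce. The following is an illustration only.

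Inputs from the Sample size section: 100 per arm, 30% drop-out, planned effect 0.40 SD, one-tailed alpha 0.05. That leaves 100 × 0.70 = 70 per arm.

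Assumed, not in the documents: share q of EmotionRegulation patients removed = 5%, 10% or 20%; difference D between their mean outcome and that of the rest of the arm = 0, 0.25 or 0.5 SD.

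If the retained patients have mean m, the full arm has mean (1 − q)m + q(m + D) = m + qD. Removal therefore shifts the estimate by q × D.

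| q | Left in EmotionRegulation (TAU 70) | Shift, D = 0.25 | Share of 0.40 | Shift, D = 0.5 | Share of 0.40 |
|---|---|---|---|---|---|
| 5% | 66.5 | 0.0125 SD | 3% | 0.025 SD | 6% |
| 10% | 63 | 0.025 SD | 6% | 0.05 SD | 12.5% |
| 20% | 56 | 0.05 SD | 12.5% | 0.10 SD | 25% |

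With D = 0 the shift is 0 throughout.

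Suppose the removed patients did worse and there is no true effect. The one-sided error rate in a simple comparison of means is then 1 − Φ(1.645 − qD/SE), with SE = √(1/(70(1 − q)) + 1/70).
- q = 10%, D = 0.25: SE = √(1/63 + 1/70) = 0.174, giving 6.7% instead of 5%.
- q = 20%, D = 0.5: SE = √(1/56 + 1/70) = 0.179, giving 13.9%.

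**Step 5: what would a willingness question alone achieve?** If it screened out half of the affected patients (also assumed), the remaining share is (q/2)/(1 − q/2) = 2.6%, 5.3% or 11.1%. At D = 0.25 the shift becomes 0.006, 0.013 or 0.028 SD; at D = 0.5 it becomes 0.013, 0.026 or 0.056 SD. The question reduces the removals without ending them. Keeping the patients in the intention-to-treat analysis sets the shift from this rule to zero, because nobody is removed under it.

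**The case against.** The strongest reply is that the harm comes from the data-exclusion sentence in the EmotionRegulation section, and that d) only labels the patients affected. Rewording d) alone would leave the bias in place. The medication rule shows this: an arm-neutral check before enrolment already sits beside a one-arm removal afterwards. This stands, and it is why the fix has to cover the exclusion sentences as well as the criterion.

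Two stronger readings are tempting, and neither is supported.
- A reader might infer that d) can act only by removing patients. The section first sets a prospective ban, so a patient who gives up other therapy on allocation complies and stays in. Removal follows only a breach.
- A reader might infer that nobody asks about other therapy before randomisation. The Recruitment section has the researcher confirm that the candidate understands the study and its treatment options, and a patient may accept the restriction conditionally at that point. The information sheet, handout and eligibility sheet are not shown. What can be said is that the listed criterion is not such a check.

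It may also be argued that the exclusion was meant for the per-protocol analysis. That would be sensible, but neither sentence says so. An analysis plan could settle which patients are analysed, but it cannot make d) usable at screening.

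Lastly, every figure for the size is assumed. That is correct and limits the conclusion.

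**Conclusion.** The point holds on the text. Criterion d) cannot be assessed when eligibility is settled. As written it is an EmotionRegulation-only restriction whose breach removes data, with no TAU counterpart and in conflict with the stated intention-to-treat analysis. The parallel one-arm exclusion for medication changes has the same fault.

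The size cannot be derived from the documents. Under the assumptions shown, the shift runs from 0 to 0.10 SD, or 0% to 25% of the planned 0.40. The middle case (10% removed, 0.25 SD apart) gives 0.025 SD, about 6%. If few patients take up other therapy, or if their outcomes resemble the rest, it is close to zero.

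A reader might infer that the rule is set to favour EmotionRegulation, or that a large bias is likely. The documents support neither, since the direction depends on why patients took other therapy and how they fared. Nor is the study population left undefined: the sections taken together admit patients in current therapy. The logical fault is definite, its consequence is uncertain, and the remedy is cheap.

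**What to change.** 1. **Criterion.** Replace d) with one that is checked in every candidate before randomisation: *willing to forgo other psychological treatment during the study if allocated to EmotionRegulation*. Put the same wording on the clinicians' eligibility sheet, and ask it when the diagnostic interview confirms eligibility. Current psychological treatment can be noted at baseline in both arms, for description only.
2. **Exclusion sentences.** Keep the ban in the EmotionRegulation section as an intervention rule only. Record later psychological treatment as a protocol deviation, keep those patients in the intention-to-treat analysis, and limit the data exclusion to the per-protocol analysis. Do the same for the medication-change exclusion in the Eligibility criteria.

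The first change makes the rule usable and should reduce breaches. The second removes the conflict with intention to treat. The per-protocol comparison would still exclude on a one-arm rule, but the Analysis section already acknowledges selection bias there.

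**Cost.** One reworded criterion, matching text on the sheet, one question at an existing visit, and two edited sentences. A few candidates may decline. Those unwilling to forgo therapy would be lost from TAU too, so the sample is slightly narrower in a trial that counts external validity among its strengths. The trial is already recruiting, so patients enrolled so far entered under the old wording; the second change can still cover them.

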#### Treatment as usual

Treatment as usual (TAU) is treatment as delivered in current daily practice by psychiatrists and clinical psychologists in the mental health centers in Spain. TAU may refer to psychiatric treatment, which typically includes prescription and monitoring of antidepressant and/or anxiolytic medication, psychological treatment (this may include case management, group psychotherapy, empathic listening and/or supportive counselling), or a combination of both. Patients in the TAU condition already receiving any of the aforementioned treatments are informed they will continue to receive as usual the services received before enrollment in the study.

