#### Analysis

Intention-to-treat analyses and per protocol analyses will be performed. Reporting of the results will follow CONSORT recommendations [75, 76]. First, the two groups will be compared in order to verify that there are no significant differences between them at baseline using samples t-tests for continuous distributed variables and chi-squares test of independence for categorical to confirm that they are comparable after randomization.

The intention-to-treat principle will be used when analyzing primary and secondary post-treatment data and data collected at the 3- and 12-month follow-ups using mixed effect models with full information maximum likelihood estimation. This method has been recommended for its flexibility over repeated-measures ANOVAs to handle missing date more appropriately [109].

Within and between-group changes will be computed calculating standardized effect sizes (Cohen’s d). Cohen’s d is calculated by dividing the differences between means by the pooled standard deviation [110]. An effect size of 0.20 is considered to be small, of 0.50 to be moderate, and 0.80 and above to be large [110].

Per protocol analyses (compliers only analysis) will also be conducted. Despite this procedure suffers from selection bias, it can help to draw conclusions about the maximum treatment efficacy in patients who comply fully with the treatment [111].

As the trial is still in execution, the state of the art regarding analytic methodology for RCT will be reviewed before analyzing the data, thus variations in the selection of the most appropriate analytic procedures may occur.

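### The plan removes randomised EmotionRegulation participants from analysis after a medication increase or change or other psychological treatment, with no matching TAU rule, which conflicts with its declared intention-to-treat analysis

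*Protocol article*

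**What the plan says.** All references are to the protocol article.

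- **Eligibility criteria.** On medication: "the increase and/or change in the medication during the study period in the experimental group will imply the participant’s exclusion from subsequent analyses". The rule is asymmetric within the arm, since "a decrease in pharmacological treatment is accepted". Exclusion criterion (d) reads "receiving another psychological treatment during the study in the experimental group".
- **Interventions, EmotionRegulation.** Both conditions (no medication change or increase, no other psychological treatment) are restated for this arm, followed by "Failure to fulfill these criteria will result in the participant’s data being excluded from data analysis".
- **Treatment as usual.** TAU may be medication, psychological treatment or both. "Patients in the TAU condition already receiving any of the aforementioned treatments are informed they will continue to receive as usual the services" they had before enrolment. No exclusion from analysis is attached to this arm.
- **Recruitment.** Randomisation is requested only once the patient is found to meet all study criteria.
- **Analysis.** "The intention-to-treat principle will be used when analyzing primary and secondary post-treatment data and data collected at the 3- and 12-month follow-ups", by mixed models with full information maximum likelihood. A compliers-only per-protocol analysis is described separately, without reference to the exclusions above.

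**The concern.** An intention-to-treat comparison keeps every randomised participant in the allocated arm whatever happens afterwards. The exclusions here depend on events after randomisation, act in one arm only, and concern events that plausibly mark an unsatisfactory course. If they are applied to the main analysis, EmotionRegulation loses some of its worse-faring participants while their counterparts stay in TAU. The arms are then no longer the groups that randomisation made comparable.

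Both primary outcomes are at stake, as are the secondary outcomes measured in both arms. A difference could appear where there is none, or a real one could be overstated. Criterion (d) adds to the problem: an exclusion criterion that depends on the allocated arm and on later treatment works as a rule for removing people after randomisation.

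**Working it through.** **1. The texts side by side.**

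| Question | Eligibility criteria / EmotionRegulation | Treatment as usual | Analysis |
|---|---|---|---|
| Participant with a medication increase or change | Excluded from analysis | No rule | Kept (intention-to-treat) |
| Participant with other psychological treatment | Excluded from analysis | May be part of TAU | Kept (intention-to-treat) |
| Limited to the per-protocol set? | Not stated | n/a | Per-protocol set described separately, no link |

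The first and last columns give opposite instructions for the same participant. This needs no arithmetic.

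**2. Criterion (d).** Recruitment requires all criteria to be met before allocation. Criterion (d) needs the arm and the later treatment to be known. It cannot be assessed at that moment.

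**3. Does full information maximum likelihood help?** It uses the observed data of participants with gaps. It does not bring back data that were deliberately removed. If only data after the event were dropped, the Instruments table shows no BAI or BDI-II assessment between baseline and 18 weeks. For an event in that interval, the model would then hold only the baseline score and would not see the deterioration that led to the event.

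**4. Illustration of size.** The plan gives no figure for this rule. From the Sample size section come 100 per arm, about 30% drop-out and a design effect of d = 0.40, so 100 × (1 − 0.30) = 70 per arm. The rest is assumed:
- no true effect;
- in each arm the fraction f with the worst course has the event, and these are removed from EmotionRegulation only;
- course and outcome are normal with correlation r = 0.3 or 0.5;
- the added treatment gives a benefit of b SD, first set to 0.

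With z the upper-f normal quantile and φ the normal density:

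spurious d = r·φ(z)/(1 − f) − b·f

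For f = 10%, r = 0.5, b = 0: φ(1.28) = 0.1755, and 0.5 × 0.1755/0.90 = 0.098.

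The rejection rate uses SE = √(1/70 + 1/(70(1 − f))). For f = 10% the SE is 0.174, and the one-sided rate is 1 − Φ(1.645 − 0.0975/0.1737) = 0.139.

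| Excluded f | Spurious d, r = 0.3 to 0.5 | Rejection, one-sided 5% | Rejection, two-sided 5% |
|---|---|---|---|
| 5% | 0.03 to 0.05 | 7% to 9% | 5% to 6% |
| 10% | 0.06 to 0.10 | 10% to 14% | 6% to 9% |
| 20% | 0.11 to 0.18 | 14% to 25% | 9% to 16% |
| 30% | 0.15 to 0.25 | 20% to 38% | 13% to 27% |

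Simulation under the same model agrees with the spurious d and the one-sided column to rounding.

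**5. Sensitivity to direction.** Setting d = 0 gives a break-even benefit b = r·φ(z)/(f(1 − f)). Over f = 5-30% this is 0.65 down to 0.50 SD at r = 0.3, and 1.09 down to 0.83 SD at r = 0.5. At f = 20% and b = 0.5, the spurious d falls from 0.105 to 0.005 (r = 0.3) and from 0.175 to 0.075 (r = 0.5). If the events are unrelated to course (r = 0) and b = 0, there is no bias.

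**The case against.** The best defence is that the conflict is one of drafting. The Eligibility section speaks of later analyses, which could mean that only data after the event are dropped. The article also announces a compliers-only analysis, and if the exclusions were meant to define that set, both statements could be followed. The document does not rule this intention out, so a reader should not take removal from every analysis as settled. But neither exclusion statement names the per-protocol set, and "Failure to fulfill these criteria will result in the participant’s data being excluded from data analysis" carries no limit of time or analysis. Even the narrower reading discards data that intention-to-treat would keep. The note that analytic procedures may be revised does not withdraw the rule.

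The second objection is to direction and size, and much of it stands. The document nowhere says that these participants fare badly. A change could be a switch for side effects, and effective added treatment reduces the bias or could reverse it. The rejection rates depend on sidedness: the one-tailed test is stated for the sample size, and the Analysis section does not fix it.

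A reader might also infer three further harms that the document does not support:
- **Every secondary outcome is biased.** OASIS, ODSIS and PANAS are collected after program modules, and the expectation scale at the end of the program's welcome module. These offer no between-arm comparison to distort.
- **The 12-month result suffers most.** The study period in the exclusion rule is not defined, and no calculation shows this.
- **Power falls materially below plan.** Those excluded may overlap with the 30% drop-out already allowed for.

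**Conclusion.** The concern holds as a contradiction in the plan: a one-arm exclusion from analysis after randomisation, stated twice without limit to an analysis set, against a declared intention-to-treat analysis. This conclusion rests on the text alone.

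That the rule would favour EmotionRegulation is likely, not established. It assumes that increases, changes and added therapy mostly follow poor response and that the added treatment does not fully make up for it. Under the illustrative assumptions the artefact is about 0.03-0.25 SD, that is 0.03/0.40 ≈ 8% to 0.25/0.40 ≈ 63% of the design effect. The event rate, the correlation and the zero benefit are all assumptions. Because the rule touches both primary outcomes, it should be resolved before any analysis.

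**What to change.** - Delete the exclusion-from-analysis sentences in Eligibility criteria and in the EmotionRegulation section, or state in both places that they apply only to the per-protocol or a sensitivity analysis.
- State in Analysis that the intention-to-treat analysis includes every randomised participant as allocated, with all collected data, whatever medication or psychological treatment followed.
- Keep assessing these participants at post-treatment and both follow-ups, and record medication changes and other psychological treatment in both arms.
- Reconcile criterion (d) with the Recruitment, EmotionRegulation and Analysis sections, so that it is clear what is checked before randomisation and what is a later event. This leaves the concomitant-treatment rule itself unchanged.

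The cost is an amendment to the wording, continued assessment of participants who would otherwise have been set aside, and a log of concurrent treatment in both arms. The article reports the trial as still recruiting, so at that stage the data could still be kept. The estimated effect may come out somewhat smaller.
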